## Study protocol

### Filter Questions

1 Is your study considered research as defined in the guidance icon information?

☒ Yes ☐ No

2 Does your study require any of the following external ethical reviews? NHS REC; Social Care REC or Ministry of Defence REC

*See guidance icon for further information on NHS REC, Social Care REC and MOD REC review remit.*

☐ Yes

☒ No

### Data Collection

3 Select one category from the list below (categories are defined in the guidance icon).

My study involves:

- ☒ a) Only primary data collection involving human subjects.
- ☐ b) Use of identifiable human subject data that is not in the public domain. This includes analysis of previously collected data (including human tissue) and/or the use of existing data that has not previously been used for research purposes (such as data taken from private social media groups)
- ☐ c) Both primary data collection involving human subjects and the use of identifiable pre-existing human subject data not in the public domain, as outlined above
- ☐ d) Data collection not involving any of the above but presenting sensitive issues
- ☐ e) None of the above

#### 4 Risk Checklist: Please indicate if your study involves any of the following risks:

- ☐ a) The research involves participants who are vulnerable or unable to give informed consent or in a dependent position.
- ☐ b) Participants will take part in the study without their consent or knowledge at the time of participation or deception of some kind will be involved.
- ☐ c) The research topic may lead participants to disclose their involvement in activities that are illegal, could make them the target of personal or professional reprisals, or otherwise represent a threat to themselves or others.
- ☒ d) The study may induce psychological stress or anxiety, or produce humiliation or cause harm or negative consequences beyond the risks encountered in a participant's usual everyday life.
- ☐ e) Participation in this research may identify urgent mental health risks, including, but not limited to, suicidal ideation and/or self-harm intent.
- ☐ f) There is a foreseeable likelihood that a participant's capacity to give fully informed consent may diminish throughout the course of the project i.e. early stage dementia, brain injury etc.
- ☐ g) The study involves imaging techniques such as MRI scans or ultrasound.
- ☐ h) The study involves sources of non-ionising radiation (e.g. lasers)
- ☐ i) The study involve physically invasive procedures or the collection of bodily materials (including collection of human tissue for purposes such as DNA/RNA analysis)
- ☐ None of the above.

#### 5 Does the study involve the recruitment of participants under the age of 16?

- ☐ Yes
- ☒ No

#### Based on your answers to the above filter questions your research has been categorised as High Risk

You can now access an overview of the available sections of the application by selecting the navigate tile in the action panel on the left. Alternatively you can proceed through each section of the application by selecting the next tile.

Upon submission will be subject to review at the next relevant Research Ethics Subcommittee meeting. Meeting dates and submission deadlines can be found [here](#)

## Section A: General Information

### A Applicant Details

First Name

Surname

Department

KCL Email

A2 Applicant Status

MPhil / PhD/ Specialist Doctorate

A5 Is King's College London the lead research sponsor?

☒ Yes ☐ No

A7 Faculty/Institute/School

*Please refer to the information icon if you are unsure of your Faculty/Institute/School.*

Nursing and Midwifery

A8 Course/Qualification

MPhil/PhD

Section B: Project Information

B1 Project Title  
A working title that accurately reflect the aims of the project.

Empowering Parents to Optimize Feeding Practices (EPO Feeding): a Feasibility and Acceptability Randomized Controlled Trial

B2 Anticipated start date for the collection of data: 04/12/2023

B3 Expected completion date of the project: 17/03/2024

B4 Is this a funded project?

- ☐ Yes
- ☐ No

B5 Please provide a summary of your project aims and objectives written in lay language that will be easily understandable to non-academic readers and non-specialists in your field. This summary should ideally be prefaced by the research question you hope to investigate in relation to your project, hypotheses to be tested, as well as a brief explanation of the academic background to the study.

*Please Note: Applications to the Health Faculties RESC should include a full list of references/citations to back up the academic/scientific justification of the project.*

#### Background and Rational

Feeding practices refer to specific practices or strategies that caregivers employ to manage what, when, and how much their children eat and to shape their children's eating (Boots, Tiggemann, & Corsini, 2018; Vaughn, Tabak, Bryant, & Ward, 2013; Ventura & Birch, 2008). There are two types of feeding practices: non-responsive and responsive feeding practices (Jansen, Williams, Mallan, Nicholson, & Daniels, 2018; Savage, Rollins, Kugler, Birch, & Marini, 2017; Shi et al., 2017). Non-responsive feeding practices (also known as coercive control), such as pressure to eat, restriction of food, and use of food as a reward (Vaughn et al., 2016), have been the most studied and raised concerns owing to their close links with children's obesity (Beckers, Karssen, Vink, Burk, & Larsen, 2021; Boucheron & Bhopal, 2020; Dev, McBride, Fiese, Jones, & Cho, 2013; Faith, Scanlon, Birch, Francis, & Sherry, 2004; Ruzicka, Darling, & Sato, 2020). Positive relationships between non-responsive feeding practices and child weight status have been consistently reported (Beckers et al., 2021; Ruzicka et al., 2020). A recent meta-analysis of 51 studies, with 17431 parent-child dyads reported that the use of controlling feeding practices by caregivers was associated with a greater risk of child obesity (Ruzicka et al., 2020). In contrast, responsive feeding practices have been identified as having a protective effect against childhood overweight and obesity and are associated with reduced risk of overweight and obesity (Adams et al., 2018; Matvienko-Sikar et al., 2018). Unlike adults, children cannot choose the environment in which they live or the food they eat. Caregivers' feeding practices are therefore critical in shaping children's eating habits and are a key target in efforts to reduce childhood overweight and obesity (Golan & Crow, 2004; Moore, Tapper, & Murphy, 2010). However, the findings from our systematic review showed that few studies focused on optimizing/changing caregivers' feeding practices with preschool children and used them as primary outcomes. It may be attributed to their interest in child nutritional-related variables (e.g., obesity prevention and management and child healthy eating promotion) in most articles (Hart et al., 2016; Haines et al., 2016; Leung et al., 2014). Therefore, there is a need to develop an intervention program focused on the most effective ways to optimize feeding practices.

Due to their close link to childhood overweight and obesity, many studies have examined factors related to feeding practices (Chang, Mendelsohn, Fierman, Au, & Messito, 2017; Eichler & Schmidt, 2019; Francis, Hofer, & Birch, 2001; Freitas et al., 2019; Robertson, Dempster, Doherty, & Sharpe, 2022; Ruzicka et al., 2020). Recent studies have reported that caregivers' perception of child weight (weight perception) is associated with their feeding practices, which has been also confirmed in my previous cross-sectional study (Wang et al., 2022). However, research has shown that caregivers of young children do not perceive overweight or obesity as a health threat (Doolen, Alpert, & Miller, 2009; Rietmeijer-Mentink, Paulis, van Middelkoop, Bindels, & van der Wouden, 2013). Instead, they prefer chubby children and tend to use food as an educational and emotional tool (Jiang et al., 2007). Recent findings reported a high percentage of misperception of child weight, with caregivers tending to underestimate children's weight, especially in low social economic areas (Lundahl, Kidwell, & Nelson, 2014; Queally et al., 2018; Rietmeijer-Mentink et al., 2013; Wang et al., 2022). In China, where mothers or grandparents are commonly the primary caregivers of children, studies have reported over half of the caregivers underestimated the actual weight of their overweight children (Wang et al., 2022). More problematic, when caregivers cannot recognize their preschool children's weight problems, they may not implement effective feeding practices to control their children's weight. In addition, targeting interventions on caregivers' misperception of their child's weight has already been confirmed to be effective (Flores-Peña, He, Sosa, Avila-Alperez, & Trejo-Ortiz, 2018; Gomes, Barros, Pereira, & Roberto, 2018; Zacarias, Shamah-Levy, Elton-Puente, Garbus, & Garcia, 2019). Thus, there is a need to include the component of improving caregivers' accurate perception of child weight as one of the components of intervention on optimizing their feeding practices.

The aim of the whole project is to develop and test the feasibility of an intervention to improve caregivers' perception of preschool child weight and their feeding practices in China.

Research on using qualitative methods for feasibility and acceptability RCT will be likely of particular importance in refining understanding of how the intervention works and facilitating ongoing adaptation of intervention and evaluation design in preparation for a full trial. Thus, this study will nest a process evaluation, including semi-structured interviews and observation of modules, which aim to extend an in-depth understanding EPO Feeding intervention program for this feasibility and acceptability trial.

- 1) Semi-structured interviews will be conducted for participants and healthcare professionals who delivered the intervention modules. A topic guide (Appendix 1: interview topic guide) was developed by the research team to address the research questions.
- 2) The researcher (JW) will observe each module, which aims to expand the immediate response and feedback for each module

and to assess the level of intervention fidelity. The researcher (JW) will also make fieldnotes about the module delivery and response to the modules provided on the program, barriers and enablers of the program completion, participants' task engagement, and its overall structure, delivery, and content of the program (Appendix 2: Observation checklist).

3) All modules will be video/audio recorded by a facilitator and checked by two researchers (XXW and JW) to rate against the fidelity checklists and ensure modules are delivered as intended (Appendix 3: Fidelity checklist).

## 2. Quantitative data/outcomes

-The primary objectives (i.e., the feasibility and acceptability of the EPO Feeding program) will be collected. These included data on recruitment and retention, adherence, and the feasibility of the outcomes which are described below:

### Recruitment and retention

- Number of eligible participants approached and consenting to take part, which is randomized, as well as the number of ineligible participants.

- Number of participants who successfully complete modules
- Number of participants lost due to follow-up and dropout rate.

### Attendance/Adherence

- Number of (each) modules attended.
- Number of homework/assignments finished.

### Acceptability

- An anonymous survey containing eight closed questions (e.g., How would you rate the quality of the program? How valuable was the program in helping you optimize feeding practices?) and one open question (i.e., comments on the experiences or feelings about EPO Feeding program) after the intervention. The survey for acceptability is uploaded (Appendix 7 English version)

-The secondary objective is to test the potential effects of EPO Feeding program. These data will be collected at the baseline and follow-ups. The questionnaires for baseline and follow-up are uploaded (Appendix 4 and 5).

- Demographic and socioeconomic data including children's age, sex; caregivers' role, age, weight, height, education level and household annual income, and number of children will be collected at baseline only.

- Parental feeding practices The Chinese Preschoolers' Caregivers' Feeding Behavior Scale (CPCFBS) will be used to evaluate parental feeding practices [1]. The CPCFBS assesses two types of non-responsive feeding practices: four items of content-restricted feeding (strict limitations on the children's access to foods or opportunities to consume unhealthy foods [2]), three items of pressure to eat (insists, demands, or physical struggles with the child in order to get the child to eat more food [2,3,4]), and three types of responsive feeding practices: four items of monitoring (the extent to oversee their child eating [3]), six items of encouraging healthy eating (the behaviors of encouraging their children to eat more healthy food [1]) and seven items of modelling (modelling of healthy food choice to encourage children to adopt similar behaviors [1]). Two items of use of food as a reward (use of desired food as a method to regulate child eating or behaviors) will be assessed using the Chinese version of the Child Feeding Questionnaire (C-CFQ) [5]. Each item of CPCFBS and C-CFQ is rated on a 5-point Likert scale. The response options for each item are "always," "usually," "sometimes," "rarely," and "never". Each subscale is calculated by averaging the scores of all the items in that subscale.

- Parental perception of preschool child weight (i.e., self-reported and visual perception) The Chinese version of the Child Feeding Questionnaire (C-CFQ) [5] will be used to measure the self-reported perception of child weight by asking to describe their child's weight status from 5 response options: "underweight", "a little underweight", "about the right weight", "a little overweight", or "overweight" (by words). Parental visual perception of child weight will be assessed by the Parents' Perception of Healthy Weight (PPHW) in the age range 2 to 6 years old [6]. The use of PPHW has been supported conceptually [7] and empirically by studies [8, 9] on the Asian population. The parent will be asked to select one gender an appropriate image/sketch that most closely matches the child's body type on a 7-point scale (1 = a severely underweight child, 4 = an average weight child, 7 = an obese child).

- Parenting Sense of Competence The Chinese version of the Parenting Sense of Competence Scale will be used to assess parental perception of their abilities to manage the demands of parenting [10, 11]. It includes two subscales: 8 items in the Efficacy measuring parental perception of competence in the parenting role and 9 items in the Satisfaction subscale assessing parental satisfaction and comfort with the parenting role [10]. Each item is rated on a 6-point Likert scale, from "Absolutely disagree" to "Absolutely agree". Each subscale is calculated by averaging the scores of all the items in that subscale.

- Child eating behaviors Five common types of child eating behaviors will be assessed by the Chinese Preschoolers' Eating Behavior Questionnaire (CPEBQ) [12], which includes five items of food fussiness (reluctance to try new food or eating limited food [12, 13]), six items of food responsiveness (the desire to eat food when children see or smell food, or were supplied with food [12, 13]), five items of satiety responsiveness (the limited amount of food the child eats in a meal [12, 13]), four items of unhealthy eating habits (the behaviors of child chewing, swallowing, spitting out or throwing, etc. [12]) and five items of initiative eating (the ability of child independent eating [12]). Each item was rated on a 5-point Likert scale. The response options for each item are "always," "usually," "sometimes," "rarely," and "never". Each subscale is calculated by averaging the scores of all the items in that subscale.

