##### - Quantitative data

Demographic and socioeconomic data including children's age, sex; caregivers' role, age, weight, height, education level and household annual income, and number of children will be collected at baseline only. A survey related to the trial acceptability will be assessed immediately after the intervention (Appendix 7). Quantitative data including parental feeding practices, perception of child weight, parenting sense of competence; and child eating behaviors will be collected from participants at three-time points: baseline (T0), immediately after the intervention (T1), and one month after the intervention (T2). The kindergarten healthcare staff who is unaware of participants' group allocation will be trained to distribute and collect the questionnaires and measure children's weight and height at each time point in the kindergartens. The questionnaire will take approximately 15 minutes.

The questionnaire also includes some identified information: preschool child student ID number, participant contact details (phone number). We need to assess child's actual weight and height at the kindergarten at each time point after getting the approval of kindergarten gatekeeper. Except for baseline assessment (T0), parents in the intervention group will receive text messages about their preschool child's actual weight status a week before the assessment of each time point from a kindergarten healthcare staff who is not involved in collecting child weight and height and is not blind to group allocation. We will also use child's actual weight status to compare with parental self-reported and visual perception of child's weight separately and then, we can calculate the prevalence of parental misperception of child's weight in this sample.

The included scales have been all used in the Chinese sample and showed moderate to good internal consistency reliability in existing studies including my previous study [2]. The questionnaire is attached in the additional file (Appendix 4 and 5).

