##### - Qualitative data

After completion of modules, the participants will be sent an invitation for semi-structured interview via WeChat messages. If some participants drop out, the researcher (JW) will first send messages to them via WeChat and then ask if they could be interviewed online. If they agree, the semi-structured interview will be conducted after receiving their written informed consent. An interview indicative topic guide (Appendix 1) is informed by the objectives of feasibility and acceptability which will guide the qualitative data collection. Interviews will take place on the kindergarten premises or via phone/WeChat call and will last about 40 min. Two healthcare professionals in the local maternal and child health hospital where we will register our study will deliver the intervention program but will be included in the process evaluation (semi-structured interviews).

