#### Data analysis

##### - Quantitative data analysis

The primary objectives of this feasibility and acceptability RCT will be addressed via descriptive estimates (e.g., means, standard deviations, and percentages). Measurements of study feasibility include recruitment rate, rates of intervention compliance, and participant retention rates. The total number of participants included in each attendance and assessment will be reported to account for missing data. The retention rate will be calculated as the rate of completion of one-month follow-up. The feasibility of collecting quantitative outcome data includes < 20% missing data at the group level at each time point. The acceptable proportion of enrolled participants who complete all modules will be 80% or greater, given that there's 10%-16% dropout rate of participants in some related RCTs [3,4, 5]. Participants will also rate five elements of the intervention on a 10-point Likert scale will be used to test the acceptability of the intervention. Participant acceptability of the intervention will be considered by a score of six or more, unacceptability will be regarded when participants scored five or less on the Likert scale.

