Next, we will ask permission to place a box in the kindergarten's waiting areas for five working days (8.00 AM-5.00 PM every day) three times after the kindergarten healthcare staff distribute the consent form and baseline questionnaires (the first time), questionnaires/survey immediately after intervention (the second time) and questionnaires one-month follow-up (the third time) within a regular date (around two working days each time) at the kindergarten's waiting areas (4.30-5.30 PM off-school period) so that parents can return the consent form and questionnaires. This healthcare staff will check the box every day and collect the returned consent form and questionnaires.

Finally, we will request permission from gatekeepers at kindergartens to book/provide a kindergarten conference room/other available premise for intervention modules and semi-structured interviews (process evaluation).

The gatekeeper will not be aware of who participates in the whole process.

-We will also obtain permission from the parents of children that the kindergarten healthcare staff will assess their child's height and weight at each time point via the student ID they write on the questionnaire after receiving their consent form.

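### The acceptability figure describes only parents who return an anonymous survey, with no place in the rule for those who give no score and no link to the attendance record

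*Protocol*

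**What the plan says.** Protocol B8, under Acceptability, describes the measure as "An anonymous survey containing eight closed questions" and one open question, given after the intervention. B9, under Data collection, fixes the timing: "A survey related to the trial acceptability will be assessed immediately after the intervention (Appendix 7"). C6b describes how forms travel: kindergarten healthcare staff hand out the "questionnaires/survey immediately after intervention (the second time") over about two working days, and parents return them to a box left out for five working days.

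B9, under Quantitative data analysis, gives the scoring: "Participants will also rate five elements of the intervention on a 10-point Likert scale", and "Participant acceptability of the intervention will be considered by a score of six or more", with five or less counted as unacceptable. No denominator is named, and parents without a score are not mentioned. The same section says the number of participants in each assessment will be reported.

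For parents who drop out, B9, under Qualitative data, plans a WeChat message and then to "ask if they could be interviewed online". The interview guide "is informed by the objectives of feasibility and acceptability which will guide the qualitative data collection". C1 sets the number of parent interviews at 10 to 12.

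B8 records modules attended. The outcome questionnaires carry the child's student ID and a phone number (B9, Data collection). The survey is described as anonymous.

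**The concern.** Whether a parent returns a voluntary form handed out when the programme ends plausibly depends on how much that parent liked it. If so, losing dissatisfied parents raises the share scoring six or more, and the rule has nothing to offset this. Reporting how many forms came back shows the size of the gap. It does not show whose forms are missing, or whether low attenders rated the programme lower.

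A stated purpose of the trial is to refine the programme, and the ratings most useful for that come from parents who stopped attending. Anonymity, the missing link to attendance and the lack of a described survey step for dropouts are choices about data collection. Once the forms are in, no later analysis can restore what was not collected.

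**Working it through.** **Inputs from the protocol**
- Target of 70 parents, 35 per group; 20% loss to follow-up; at least 56 completing (C1).
- Score of six or more counts as acceptable (B9, Quantitative data analysis).
- Dropout of 10%-16% in related trials; criteria of 80% or more completing all modules and less than 20% missing outcome data (same section).

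**The plan's own figure.** 56 / (1 - 0.20) = 70, so the recruitment target reproduces.

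**Assumptions.** The protocol gives no return rate for the survey. Its 20% is loss from the study, and is used here only as a convenient value: 35 × 0.80 = 28 forms, 7 not returned. The 24 scoring six or more is also assumed. I take the five rated elements to belong to the anonymous survey, because no other acceptability instrument is described; B8 speaks of eight closed questions, and the two passages should be reconciled.

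**Bounds.** Let x be the number scoring six or more, r the forms returned and n = 35 randomised to the programme.
- Among returners: x / r = 24 / 28 = 86%.
- Lower bound over all randomised (every non-returner unfavourable): x / n = 24 / 35 = 69%.
- Upper bound (every non-returner favourable): (x + n - r) / n = (24 + 7) / 35 = 31 / 35 = 89%.

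The width of the range is (n - r) / n, here 7 / 35 = 20 percentage points, whatever x is.

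**Other assumed values**

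| Returned | Scoring six or more | Among returners | Range over 35 randomised |
|---|---|---|---|
| 28 | 28 | 100% | 80.0% to 100% |
| 28 | 25 | 89.3% | 71.4% to 91.4% |
| 28 | 22 | 78.6% | 62.9% to 82.9% |
| 32 | 29 | 90.6% | 82.9% to 91.4% |

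With 3 of 35 forms missing, the width falls to 3 / 35 = 8.6 points.

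**Linkage.** Attendance is recorded per module and the outcome questionnaires carry a student ID. An anonymous survey carries no key to either, so ratings cannot be matched to attendance records, and parents who returned no form cannot be matched to those who dropped out.

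**The case against.** Several points on the other side are sound.

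- **Dropouts are not shut out of the survey.** A reader might infer that parents who stopped attending are approached only for an interview. C6b hands the survey out in the same round as the post-intervention questionnaires and does not limit it to attenders, and the intention-to-treat paragraph keeps parents who do not complete the programme in the analysis. What the text fixes is that the figure reflects those who return the form. That these are mainly parents who stayed is likely, but is not stated.
- **Appendix 7 is not shown.** A reader might infer that ratings cannot be related to attendance at all. The form may already ask parents how many modules they attended. Only the link to the attendance record is ruled out.
- **Acceptability is not read alone.** Module completion is judged against enrolled participants, missing outcome data has its own limit, and dropout is reported. A programme that drove many parents away would show it there. This stands in part: with 3 of 35 forms missing because those parents dropped out, completion could still be 32 / 35 = 91%, above the 80% criterion, and the acceptability range would still be 8.6 points wide.
- **Dropouts' views are sought by interview.** This can give reasons for leaving, but within 10 to 12 interviews, and an interview does not enter the six-or-more figure.
- **Anonymity is defensible.** It protects against answers given to please, in a setting where the protocol itself acknowledges the gatekeeper's influence. The fix therefore keeps it.

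**Conclusion.** The point holds as a cheap improvement to how a primary objective is measured and reported. The acceptability result describes returners only; the rule has no place for parents with no score; and the only step described for dropouts leads to an interview. The bias is upward if dissatisfied parents return fewer forms, which is plausible but cannot be shown from the document.

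The illustration gives 86% among returners and 69% to 89% over those randomised. A reader might conclude that the true figure is 69%. That is only the lower bound: it counts every non-returner as unfavourable, and the full range includes 86%. The return rate and the 24 are assumptions. The protocol also sets no required percentage of parents scoring six or more, so moving within this range crosses no stated threshold. What changes is how far the figure can be trusted to describe everyone offered the programme.

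**What to change.** 1. In B9, Qualitative data: send the same anonymous survey, as a link, with the WeChat message already planned for parents who drop out, and ask that each parent answer only once.
2. In B9, Quantitative data analysis: report the number scoring six or more among returners and, beside it, over all parents randomised to the programme, with non-returns shown as lower and upper bounds. This needs only the number randomised and the number returned, so anonymity is untouched.
3. If Appendix 7 does not already ask it, add one coarse item on modules attended, for example fewer than 3 versus 3 or more, which is the cut-off already used for the completers analysis. Ratings can then be described by attendance.

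The cost is one link in a planned message, one line of results and at most one survey item. The downsides are a wider or less favourable figure and slightly less anonymity if few parents are low attenders; a two-category item limits the latter.
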